### Harms

In our study, adverse events (AEs) will be defined as an unexpected medical problem that happens during the course of the study related or unrelated to the intervention or assessments. All AEs occurring after informed consent is signed and until study completion will be recorded. An AE that meets the criteria for a serious adverse event (SAE) will be reported to the Ohio University IRB as a SAE. A SAE is defined as an unexpected medical problem that is believed by the investigators to be causally related to the study intervention or assessments and results in any of the following: a life-threatening condition, severe or permanent disability, prolonged hospitalization, or death. Prior to each exercise session the exercise supervisor will perform a brief medical safety check and will ask the subject if they experienced any health issues since the last exercise session. Any issues will be recorded and reviewed by the project manager. The issue will then be recorded as an AE, and will be noted if the project manager believes the issue is related to the intervention (e.g., muscle soreness).

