
### Randomization

Subjects will be randomized in a 1:1:1 ratio to receive a 12-week exercise program consisting of either resistance training (RT), moderate-intensity continuous training (MICT) on a stationary bicycle, or HIIT on a stationary bicycle. Due to the small sample size in each arm, permuted-block randomization will be used via computer-generated random numbers to ensure equal sample size. Specifically, we will create blocks of three with each treatment permuted within each block. The study subjects will be enrolled and assigned to their respective interventions by an unblinded project manager.

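### Because an SAE must be unexpected and judged causally related, a death or life-threatening event judged unrelated is recorded as an AE but is not classed or reported to the IRB as an SAE

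*Protocol article*

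**What the plan says.** All the relevant definitions are in the Harms section of the protocol article.

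- **AE.** An AE is "an unexpected medical problem that happens during the course of the study related or unrelated to the intervention or assessments". All AEs from consent to study completion are recorded.
- **SAE, first part.** An SAE is "an unexpected medical problem that is believed by the investigators to be causally related to the study intervention or assessments".
- **SAE, second part.** The sentence continues: "and results in any of the following: a life-threatening condition, severe or permanent disability, prolonged hospitalization, or death".
- **Reporting.** "An AE that meets the criteria for a serious adverse event (SAE) will be reported to the Ohio University IRB as a SAE".
- **Session check.** Before each exercise session the supervisor asks about health issues. Any issue is recorded and reviewed by the project manager. It is then entered as an AE, and it "will be noted if the project manager believes the issue is related to the intervention (e.g., muscle soreness").

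Two other sections bear on who makes these judgements. Blinding says that neither subjects nor staff can be blinded, and that only the outcomes assessor and data analyst work with coded group information. Randomization says that subjects are "assigned to their respective interventions by an unblinded project manager".

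**The concern.** Seriousness describes what happened to the subject. Causality and expectedness are opinions about why it happened and whether it was foreseen. When all three are conditions for one label, the label stops identifying serious events. It identifies the serious events that someone also judged unexpected and related.

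This matters here because the Discussion names AEs as the largest potential problem of the study and cites cardiac arrests during HIIT and MICT in cardiac rehabilitation. The trial is also meant to inform a larger one. An SAE listing that can be empty although a subject died or had a life-threatening event would be a poor basis for oversight or for planning that trial. The causality opinion is formed by people who know the arm, in a study whose stated hypothesis favours HIIT.

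**Working it through.** No arithmetic applies to the definition itself. It depends on no alpha, power, effect size or sample size. The check is to write it as a rule and apply it to cases.

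**The rule as printed**

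- AE = unexpected, whether related or unrelated.
- SAE = unexpected AND believed related AND (life-threatening OR severe or permanent disability OR prolonged hospitalisation OR death).
- Reported to the IRB as an SAE = meets the SAE rule.

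**Applied to cases**

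| Event | Meets AE definition? | SAE? | Reported to IRB as SAE? |
|---|---|---|---|
| Unexpected death, judged related | Yes | Yes | Yes |
| Unexpected death, judged unrelated | Yes | No | No |
| Life-threatening event, judged related but regarded as expected | No, read literally | No | No |
| Short new hospital admission, unexpected and related | Yes | Unclear | Unclear |
| Muscle soreness raised at a session check | No if regarded as expected; yes under the session-check procedure | No | No |

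Row 2 is the main gap. The outcome is the same as in row 1, and only the causality opinion differs.

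Row 3 follows from requiring unexpectedness in both definitions. If the subject survives and mentions the event at a later session check, that procedure would still enter it as an AE, but not as an SAE.

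Row 4 arises because the only hospitalisation criterion can mean a long stay or an extended stay. A long new admission is covered on the first reading. A short one is not clearly covered on either.

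Row 5 is a conflict within the section. The definition filters on expectedness and the session-check procedure does not. A foreseeable training effect is the procedure's own example.

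**Does any other section widen the rule?** No.

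- Intervention Discontinuation mentions serious side effects, with heart attack and exercise-related injury as examples, but only as grounds for ending participation.
- Exercise Intervention has a study physician clear health changes before training resumes, but the physician does not classify events.
- Statistical Methods does not mention AEs or SAEs.

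**The case against.** The strongest case on the other side has five parts.

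1. **Unrelated events are not lost.** AEs include unrelated ones and all are recorded, so an unexpected death judged unrelated stays in the data. This stands. The gap is in serious classification and in reporting as an SAE. The article also does not say that other AEs are withheld from the IRB, and the IRB's own rules are not shown.

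2. **No safety comparison exists to be biased.** A reader might infer that a between-arm safety comparison is biased low. The documents do not support that, because no AE or SAE analysis is stated and no listed outcome is a safety endpoint. What is affected is oversight and descriptive reporting.

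3. **The project manager does not decide SAE status.** A reader might infer that the unblinded project manager does. The SAE sentence gives causality to the investigators. The project manager notes relatedness for issues raised at session checks. The point that survives is narrower: the SAE judgement is made by staff who, under Blinding, cannot be blinded. That is unavoidable in supervised exercise, but it is also a reason not to make seriousness depend on the judgement.

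4. **The expectedness filter may rarely act.** The document has no list of expected events, and the session check captures issues without the filter. This stands as to frequency. The two statements still conflict.

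5. **Serious events should be rare.** The Discussion gives 1 complication per 23,182 HIIT exercise hours in cardiac rehabilitation. HIIT durations in Table 5 sum to 240 + 210 + 270 = 720 minutes, or 12 hours per subject. For 10 subjects that is 120 hours, and 120/23,182 is about 0.005 expected events. The figure covers training-related cardiac complications only. It says nothing about the events judged unrelated, which are the ones the rule removes.

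**Conclusion.** The concern holds as a defect in a stated definition. It is not a gap that a fuller protocol or SAP could be presumed to fill. Followed as written, a death or life-threatening event judged unrelated is recorded as an AE and is neither classed as an SAE nor reported to the IRB as one. The AE definition and the session-check procedure contradict each other on expected events, and the hospitalisation criterion is ambiguous for short admissions.

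The size cannot be put as a number. One event in an arm of 8 to 10 is 1/10 = 10% to 1/8 = 12.5%, and a reader might take that as the effect on an SAE rate. It only restates the arm size, and the documents give no all-cause rate of serious events. No primary or secondary outcome, power figure or planned test is affected.

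The conclusion rests on two assumptions: that the definitions are applied as printed, and that the investigators who judge causality are among the staff described as unblinded.

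**What to change.** In Harms:

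- Delete the word *unexpected* from the AE definition, so that it agrees with the session-check procedure.
- Define an SAE by outcome alone: death, a life-threatening condition, hospitalisation or its prolongation, or disability that is severe or permanent. Expectedness and causality should play no part in the definition.
- Record expectedness and relatedness as two separate fields for every AE. If the sponsor wants them as triggers, keep them only in a rule for expedited IRB reporting that stands apart from the SAE definition.
- List all SAEs by arm descriptively, with both fields shown.

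The cost is two rewritten sentences and two case-report fields. A few more events may be classed and reported as serious. Sample size, interventions, endpoints and efficacy analysis do not change.

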## Anticipated Results

### The Dual-Benefits Hypothesis

The HIIT group will see improvements in endurance measures (VO_2_max, 6-min walk distance, isokinetic fatigue) equal to the MICT group and greater than the RT group, and improvements in muscular characteristics (isokinetic power, MVC, thigh muscle volume, VRFD, TRFD, voluntary activation) equal to the RT group and greater than the MICT group.

### Other Hypotheses

All groups will exhibit similar changes in the 4-square step test and stair climb.

The RT group will see greater improvements in grip strength than either MICT or HIIT groups.

The MICT group will see greater reductions in fat mass than either HIIT or RT groups.

## Discussion

High-intensity interval training has become a popular exercise strategy for young adults for the equivalent or greater health benefits to traditional aerobic training with only a fraction of the time commitment (30). HIIT may also be a highly beneficial exercise strategy for older adults with potential to elicit both muscular and cardiorespiratory adaptations. However, there have been few studies assessing the effects of HIIT in older adults, with the majority being performed in individuals with overt health conditions (33, 35). Although a preliminary study, this is, to our knowledge, the first randomized controlled trial to compare muscular and cardiorespiratory adaptations of bicycle HIIT to adaptations seen in response to traditional bicycle aerobic training or resistance training in generally health older adults. Schjerve et al. (52) compared the effects of HIIT, MICT, and RT in middle-aged, obese adults, reporting large improvements in VO_2_max but no strength gains in the HIIT group. However, this study used a walking protocol for both MICT and HIIT groups, and we postulate the lack of effect on strength was due to the lower levels of muscular activity and force associated with this protocol [e.g., there is evidence that >60% of maximal muscle force must be produced during training to see increases in muscle size and/or function (22)]. HIIT has already been demonstrated to improve cardiorespiratory fitness equal to, or greater than, MICT in older adults (33, 38). Therefore, we propose in this study to determine if HIIT can produce muscular adaptations similar to those seen in response to resistance training. We will be using a cycling protocol for the HIIT group, as improvements in strength and power have been demonstrated in response to HIIT cycling protocols in young adults (28, 30).

The largest potential problem that could arise throughout the course of the study relates to the possibility of AEs. The risk of cardiovascular events in adults participating in HIIT programs is low, as reported by Rognmo et al. (66), who found that of the 4,800+ cardiac rehabilitation patients participating in either HIIT or MICT at a cardiac rehabilitation center, three suffered from cardiac arrest during training (one fatal during MICT, two non-fatal during HIIT). The rate of complications to the number of patient exercise hours was 1 per 23,182 h for HIIT (66). The target population for the current study will include insufficiently active older adults, but those with certain known heart conditions will be excluded from the study, and any subjects who display specific irregular cardiac responses during the baseline GXT (Table 3) will also be excluded. As such, risk of cardiac events is expected to be lower for our population than has been reported in cardiac rehabilitation patients. The American College of Sports Medicine recognizes the risks associated with exercise, but states that the health benefits of exercise outweigh the risks (15).

This study will assess the effectiveness of a high-intensity interval cycling exercise protocol in older adults to produce both cardiorespiratory and muscular adaptations. If shown to be effective it will pave the way for a paradigm shift from volume- to intensity-driven exercise recommendations for older adults, with the ultimate goal of improving health and reducing age-related physical dysfunction.

## Ethics Statement

### Research Ethics Approval

This study has been approved by the Ohio University Institutional Review Board (approval number: 18-F-55).

### Protocol Amendments

Any modifications to the protocol which may impact the conduct of the study, potential benefits to the subject, or affect subjects safety (including changes to study objectives, study design, patient population, sample sizes, study procedures, or significant administrative changes) will require a formal amendment to the protocol. Such amendments will be agreed upon by the principal investigators, and approved by the Ohio University Institutional Review Board prior to implementation.

### Consent

Informed consent will be obtained from each subject after the study has been fully described to the subject, and the consenting investigator believes that the subject fully understands the study requirements and can make an informed decision.

### Confidentiality

Each subject will be assigned a number and experimental data will be recorded using that number. Any identifiable personal information will be kept in a locked cabinet in OMNI, and only the PI will have key access to the information.

### Access to Data

The principal investigators will have direct access to all data sets. Data dispersed to other project team members will be blinded of any identifying subject information.

### Ancillary and Post-trial Care

There are no provisions for ancillary or post-trial care.

### Dissemination Policy

The investigators will provide the subjects with estimates of when the trial will end and when data will be published. The American Heart Association Predoctoral Fellowship requires that all journal articles be made freely available in PubMed Central within 12 months of publication. Eligibility for authorship of manuscripts resulting from this study include (1) substantial contributions to the conception or design of the project, or the acquisition, analysis, or interpretation of the data, AND (2) drafting or revising the manuscript, AND (3) final approval of the manuscript. There is no intention to use professional writers.
